# Impact of Erythropoietin in the management of Hypoxic Ischaemic Encephalopathy in resource-constrained settings: protocol for a randomized control trial

**DOI:** 10.1186/s12883-020-01751-y

**Published:** 2020-05-04

**Keywords:** Perinatal asphyxia, Hypoxic-ischemic encephalopathy, EPO and neurodevelopment

## Abstract

**Background:**

Perinatal asphyxia, more appropriately known as hypoxic-ischemic encephalopathy (HIE), is a condition characterized by clinical and laboratory evidence of acute or sub-acute brain injury resulting from systemic hypoxemia and/or reduced cerebral blood flow. HIE is a common and devastating clinical condition in resource-poor countries with poor treatment outcome. This paper describes the protocol for an ongoing study that aims to evaluate the neuroprotective effects of Erythropoietin (EPO) as compared to routine care in the management of moderate to severe HIE among term infants.

**Methods:**

This study is a double-blind randomized controlled trial that will be conducted in the neonatal wards of the Lagos University Teaching Hospital (LUTH), Lagos, Nigeria, over a two-year period after ethical approvals and consents. One hundred and twenty-eight term newborns (≥ 37 weeks gestation) diagnosed with moderate/ severe HIE at admission will be allocated by randomization to receive either EPO or normal saline. All the participants will be offered standard care according to the unit protocol for HIE. Baseline investigations and close monitoring of the babies are done until discharge. Participants are followed up for 2 years to monitor their outcome (death or neurological development) using standard instruments.

**Discussion:**

Previous trials had shown that EPO confers neuroprotective benefits and improve neurological and behavioral outcome in infants with HIE both singly or as an adjuvant to therapeutic hypothermia. This study hypothesized that administering EPO to newborns with moderate /severe HIE can positively influence their clinical and neurological outcomes and will provide evidence to either support or disprove the usefulness of Erythropoietin as a sole agent in the treatment of HIE, especially in resource-limited environment with the highest burden of the disease.

**Trial registration:**

The study has been registered with the Pan African Clinical trials registry on the 2nd of December 2018, with registration number PACTR201812814507775.

## Background

Perinatal asphyxia (PA), more appropriately known as hypoxic-ischemic encephalopathy (HIE), is a condition characterized by clinical and laboratory evidence of acute or sub-acute brain injury resulting from systemic hypoxemia and/or reduced cerebral blood flow [1]. The insult to the brain can occur in-utero, intrapartum or postnatally. Hypoxic-Ischemic Encephalopathy is the commonest etiology for neonatal encephalopathies and accounts for 23% of all term newborn deaths worldwide [2]. Severe HIE occur in 0.1–0.3% of births in resource-rich countries [2, 3]. However, the incidence of HIE is greater in low and middle-income countries (LMICs) [4] occurring in nearly 35% of neonatal admissions in India while different hospital-based studies in Nigeria documented between 2.6 and 30% [5–8]. Furthermore, Ekure et al [9] reported that HIE accounted for nearly 39% of perinatal mortalities at a tertiary hospital in Lagos, South-Western Nigeria. HIE can be mild, moderate or severe. However, the majority (about 90%) of cases of HIE that present to hospitals in Nigeria were moderate to severe [10]. The morbidity and mortality from HIE increases with increasing severity [10].

Survivors of moderate/ severe HIE have a high risk of developing severe cognitive and/or motor impairment, seizure disorders, deafness, and vision loss [11, 12] Neurologic abnormality at discharge is a strong predictor of long-term neurodevelopmental delay [13]. Many biomarkers of neurological damage resulting from asphyxia have been identified and investigated [14, 15]. Biomarkers such as nucleated red blood cells (NRBC) has been demonstrated to be markedly elevated in asphyxiated newborns and can be useful in predicting adverse neurological outcomes [13–15]. Inflammatory cytokines such as Interleukin-6 (IL-6) have been shown to accumulate early in asphyxia [16, 17]. Chiesa et al. [18] reported that IL-6 concentrations were more than 300-folds in babies with HIE as compared to normal infants. Furthermore, Creatinine kinase BB (CK-BB) has been shown to predict HIE early as its rise occurs in the first hours after brain injury [19].

Therapeutic hypothermia (HT) has emerged as the gold standard for treating HIE [20] Thus if HT is commenced within 6 hours of injury, morbidity and mortality among infants with HIE can be significantly reduced [21–24]. HT is not readily available in most LMICs such as Nigeria. It is imperative that efforts should be geared towards early diagnosis and recognition of the sequelae of HIE, and improvement in the quality of life of survivors of HIE. In Nigeria, the treatment of HIE is largely symptomatic and supportive despite the availability of beneficial treatment modalities elsewhere. Indeed, parents of babies with HIE may not be able to afford the high cost of the therapies.

Recently, some drugs such as Erythropoietin (EPO) have been found to possess positive neuroprotective, neuro-regenerative and anti-inflammatory effects in asphyxiated newborns [25–31]. EPO, hitherto widely used for Anemia of prematurity, achieves its neuroprotective effects through its anti-excitotoxic, antioxidant and anti-apoptotic effects on neurons and oligodendrocytes [25–30, 32]. It also has anti-inflammatory effects on astrocytes and microglial cells [25–28, 31]. EPO prevents NO-induced cell death, protects neurons from glutamate toxicity, [33] and has demonstrable effects on neurogenesis, differentiation and repair after injury [29, 30, 34, 35]. Several studies on human and animal models demonstrated improvement in both short and long-term neurodevelopmental outcomes among asphyxiated babies that were exposed to EPO [33, 36, 37]. Even when EPO was commenced as late as 1-week post asphyxial insult in rodents, there was still beneficial effects in behavioral outcome, neuronal protection and regeneration [38]. The systematic review by Garg et al. [39] indicated that EPO confers long-term neurodevelopmental protection on neonates with moderate/severe HIE. None of the trials conducted on EPO among newborns, have shown any significant side effect despite the high doses employed for asphyxia [33, 40, 41].

Though EPO can be used synergistically with HT, [41] studies have shown good and beneficial effects when used as a single agent in the treatment of HIE [33, 42]. This is especially important in settings where HT is non-existent or when intervention is delayed due to late presentation. Despite the poor outcome of HIE in Nigeria, there is no local evidence supporting the introduction of EPO as a routine drug for the prevention of early and late neurological complications of perinatal asphyxia in the country. This study aims to evaluate the neuroprotective effects of EPO in comparison to routine care in the management of HIE in term infants.

### Null hypothesis

Parenterally administered high dose EPO in newborns with HIE does not influence immediate or long-term outcome.

### Specific objectives

To describe the spectrum of asphyxia morbidities at the Lagos University Teaching HospitalTo compare the neurological outcomes of babies with moderate/severe HIE that had adjunctive treatment with EPO as compared to routine care in the immediate neonatal period and at 6, 12, 18 and 24 months of ageTo document common complications and adverse drug reactions in the treated infants

## Methods/ design

### Study design

This study is a double-blind randomized controlled parallel-group trial with one to one allocation ratio. The study is prospectively registered with the PACTR.

### Study setting

This study is being conducted in the neonatal wards and clinics of the Lagos University Teaching Hospital (LUTH), Lagos, Nigeria and is ongoing as at the time of this submission. LUTH is a tertiary care hospital with facilities for neonatal care. The LUTH neonatal ward is the largest in the country with a capacity to admit more than 80 babies at a time. It has inborn and out-born sections with equal capacity for admissions.

### Population and sample size

Table 1 shows the inclusion and exclusion criteria. All consecutively admitted term neonates with a diagnosis of severe perinatal asphyxia and presenting within 24 h of life in LUTH will be recruited for the study if they meet inclusion criteria.

**Table 1 Tab1:** Participants’ Inclusion and exclusion criteria for treatment

1. Enrollment criteria will include:	
• All term newborns (≥ 37 weeks gestation) diagnosed of moderate/ severe HIE at admission and who are < 24 h of age.	
• Evidence of perinatal depression based on delayed cry at birth and at least one of the following:	
1. Apgar score ≤ 3 at 5 min.	
2. Need for resuscitation at 10 min.	
3. PH < 7.1 in cord or Base deficit ≥15 mmol/L.	
4. Moderate or severe encephalopathy according to Sarnat and Sarnat staging [43]. (Table 2)	
5. History of an adverse intrapartum sentinel event such as abruptio placenta, uterine rupture, fetal distress, etc	
2. Exclusion criteria:	
• Severe congenital anomalies	
• Preterm babies	
• Infants > 24 h of age at time of presentation /consent	
• Those in which consent could not be obtained	
• Evidence of sepsis (confirmed according to unit protocol)	

### Sample size and power calculation

There was no previous study in our environment describing the efficacy of EPO administration on the outcome of HIE. Furthermore, there is a paucity of recent published data on mortality and neurodevelopmental impairment from perinatal asphyxia in our environment. Mortality rate from asphyxia was reported to be between 31.1 and 62.8% in some hospitals in Nigeria [5, 9, 10, 44]. Since no study reported the prevalence of neurodevelopmental impairment of asphyxiated babies at 2 years of life, we expected that the prevalence of a combination of the outcome of “death and neurodevelopmental impairment” at 2 years of life among moderate/ severe HIE in a resource-poor environment such as Nigeria should be higher than the prevalence of death only (31.1–62.8%). Thus, we assumed that the prevalence of “death and neurodevelopmental impairment at 2 years of life” among moderate/ severe HIE without EPO treatment in Nigeria will be about 65%. Additionally, Zhu et al. [40] in Zhengzhou, China found that 24.6% (*n* = 18/73) of babies who had EPO either died or had neurodevelopmental impairment while 43.8% who had placebo died or had neurodevelopmental impairment, giving a relative risk of 0.62 (95% CI: 0.41–0.94). Similarly, the range of protective relative risk that was reported or assumed by previous studies was between 0.65 to 0.71 [41, 45]. Hence, we utilized the power calculator in Stata version 16 statistical software (Stata Corp, USA) to calculate the minimum sample size to be 128 babies based on the assumption that 65% of infants with moderate/ severe HIE may likely die or develop neurodevelopmental impairment without treatment; assuming a protective relative risk of 0.6, 80% power and 10% loss to follow -up.

We utilized the Sarnat and Sarnat staging [43] of moderate or severe HIE for the recruitment of eligible participants (Table 2).

**Table 2 Tab2:** Sarnat and Sarnat staging [43] of moderate or severe HIE

Category	Moderate HIE	Severe HIE
1. Level of consciousness	Lethargy or obtunded	Stupor or Coma
2. Spontaneous activity	Decreased	Absent
3. Tone	Hypotonia	flaccidity
4. Posture	Distal flexion	Decerebrate state
5. Primitive reflexes		
a. Suck	Weak or biting	Absent
b. Moro reflex	Incomplete	Absent
6. Autonomic nervous system		
a. Pupils	Constricted	Deviated, dilated, or nonreactive to light
b. Heart rate	Bradycardia	Variable heart rate
c. Respirations	Periodic breathing	Apnoea
7. Seizures	Common, focal or multifocal	Absent or uncommon
8. EEG activity	Low voltage changing to seizure activity	Burst suppression to isoelectric

Presence of ≥1 of these signs in any 3 of the above 8 categories is required for diagnosis

### Risk of bias

This is a double-blind randomized control trial. Each participant is allocated into the intervention or control group by simple randomization using randomly generated number cards in sequentially numbered sealed opaque envelopes. The randomization list was created and generated online for the study by the Biostatistician based in South Africa. The outcome assessors (Paediatric Neurologist, Radiologist and the Biostatistician) are blinded to the group allocation during the study period. The managing physicians, however, are not blinded to the intervention drugs.

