### Intervention and procedure

The approach to the management of HIE in our center is supportive care. Therapeutic hypothermia is not available. Supportive care includes maintaining normothermia, fluid, electrolyte and glucose balance, respiratory support with continuous positive airway pressure (CPAP) and oxygen, control of seizures and management of other complications as they arise [46]. During this study, participants randomized into EPO group, receives 1000 IU/kg of Erythropoietin intravenously statim on admission then daily for 5 days. This dose regimen was modified from the pharmacokinetic study by Wu et al. [37] Placebo/ control group receives 2 ml of 0.9% Saline statim on admission then daily for 5 days.

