### Data and safety monitoring plan

Study data are monitored by the Paediatric Pharmacologist and the Biostatistician who are not involved with the day to day management of the recruited patients. An interim analysis for neonatal outcome is scheduled after 6 months of commencement of study in the absence of documented serious adverse effects. A decision to terminate the trial will be taken by the Paediatric Pharmacologist and the principal investigator.

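### The trial is labelled double-blind, but its treating physicians are open and the Biostatistician named as blinded appears to have made the randomisation list; as written it is outcome-assessor-blind

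*Protocol article*

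**What the plan says.** The label is given three times: in the Methods part of the Abstract, under Study design ("This study is a double-blind randomized controlled parallel-group trial with one to one allocation ratio") and under Risk of bias ("This is a double-blind randomized control trial").

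Risk of bias then sets out who knows what. On the list: "The randomization list was created and generated online for the study by the Biostatistician based in South Africa". On assessors, in the next sentence: "The outcome assessors (Paediatric Neurologist, Radiologist and the Biostatistician) are blinded to the group allocation during the study period". On treating staff: "The managing physicians, however, are not blinded to the intervention drugs".

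Other sections add the following:

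- Outcome repeats that the neurologist who assesses neurodevelopmental status is blinded.
- Cranial ultrasonography says the same of the sonologist.
- Data and safety monitoring plan gives the Biostatistician a further role: "Study data are monitored by the Paediatric Pharmacologist and the Biostatistician who are not involved with the day to day management of the recruited patients".
- Intervention and procedure doses EPO by weight, at 1000 IU/kg, while the "control group receives 2 ml of 0.9% Saline statim on admission then daily for 5 days".

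**The concern.** A double-blind label is normally read as covering those who deliver care. Here the section that applies it also denies it for the managing physicians. A fuller protocol or analysis plan could add detail, but it could not make both statements true.

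What is at stake is the claim the trial can make about bias. The primary outcome is a composite of death or neurodevelopmental impairment at 18 to 24 months. Blinded assessors protect the scoring of impairment. They cannot prevent care from differing by arm before death. Intervention and procedure and Clinical monitoring describe respiratory support, seizure control and treatment of complications as given according to need, so by judgement, and the physicians making those judgements know the arm. The secondary outcomes include time to discharge and adverse events, which may also rest with treating staff.

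The Biostatistician's position is a separate matter. On a plain reading, the author of the allocation list is named as blinded to allocation and also monitors the data.

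**Working it through.** The masking claim has no figure to recompute, so the check sets the statements side by side, first by role and then by outcome. Three short calculations follow, to show what does and does not depend on the point.

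**By role**

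| Role | Stated status | Section | Consistent? |
|---|---|---|---|
| Managing physicians | Not blinded | Risk of bias | Contradicts the label |
| Paediatric neurologist | Blinded | Risk of bias; Outcome | Yes |
| Radiologist | Blinded | Risk of bias | Yes |
| Sonologist | Blinded | Cranial ultrasonography | Yes |
| Biostatistician | Blinded, but generated the list and monitors data | Risk of bias; Data and safety monitoring plan | Unresolved |

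**By outcome**

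- Impairment at follow-up: assessed by the blinded neurologist, so protected at assessment.
- Cranial ultrasound: performed by a blinded sonologist, so protected.
- Death: objective to record, but open to influence from care given with knowledge of the arm.
- Time to discharge and adverse events: the recorder is not named. Serious adverse events says only that investigators transmit the events.
- Neurological status at discharge: Outcome places it in one series with the follow-up examinations, which suggests the neurologist. Clinical monitoring places it on the clinical-course proforma, which does not. The examiner is not named.

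**The plan's own sample size**

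Inputs from Sample size and power calculation and Statistical analysis: control rate 0.65, relative risk 0.6 (treated rate 0.65 × 0.6 = 0.39), two-sided 5%, power 80%, loss 10%.

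n per arm = [1.960 × √(2 × 0.52 × 0.48) + 0.842 × √(0.65 × 0.35 + 0.39 × 0.61)]² / 0.26² = 56.8, rounded up to 57. Then 57 / 0.9 = 63.3, rounded up to 64 per arm, or 128 in total.

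The stated 128 reproduces exactly. It does not depend on masking and needs no change.

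**How much of the primary outcome could be deaths**

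The article assumes only the composite rate, 65%. It cites mortality of 31.1 to 62.8% from asphyxia in some Nigerian hospitals. If, as an assumption, those rates applied to the control arm here, the share of composite events that are deaths would run from 31.1 / 65 = 48% to 62.8 / 65 = 97%. This shows only that the component not protected by assessor blinding could be large. It is neither a forecast nor a measure of bias.

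**The placebo volume**

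Undiluted EPO volume = 1000 × weight / concentration. The article gives neither weights nor concentration, so assume 2.5 to 4 kg:

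- at 1000 IU/ml: 2.5 to 4.0 ml
- at 2000 IU/ml: 1.25 to 2.0 ml
- at 10000 IU/ml: 0.25 to 0.4 ml

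At one fixed concentration the undiluted volume cannot be 2 ml for every infant. If each dose were made up to 2 ml, the volumes would match. The article does not say whether this is done.

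**The case against.** The strongest reply is that open clinicians with blinded assessors is a legitimate design, that the article discloses the open physicians in the same paragraph as the label, and that the impairment component is scored blind while death is objective to record. All of this stands. It makes the design defensible under its proper name, but it does not make the label correct. One might add that double-blind has no single meaning and could refer to parents and assessors. The article does not say that parents are blinded, which is a reason to name the roles.

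On the Biostatistician, the text does not state that the two mentions are one person, and a coded list could keep the analyst blind. Nor does it say who holds the list; allocation itself uses sequentially numbered sealed opaque envelopes. That reduces the point to an unresolved conflict of roles, and does not show that unblinding occurred.

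Four stronger readings are tempting and are not supported:

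- *That no real masking exists.* Blinding of the neurologist, radiologist and sonologist is stated, and nothing in the text undoes it.
- *That the fixed saline volume reveals the arm at the cot.* This depends on an EPO volume and dilution that are not given. It also adds little, since the physicians are openly unblinded.
- *That unblinded staff record adverse events, discharge timing and the discharge examination.* The recorder is not named. Several adverse events also have numerical criteria (blood-pressure percentiles on three occasions, haematocrit above 65%), which limit discretion.
- *That the trial expects mortality of 31 to 63%.* Those are reported hospital figures, not a trial assumption.

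**Conclusion.** The point holds as a contradiction about a stated design property. The trial is not double-blind as described; it is outcome-assessor-blind with open treating physicians. The Biostatistician's blinded status also conflicts, on the face of the text, with having generated the randomisation list. This second part assumes that both mentions mean the same person and that the arms are not coded; the article settles neither.

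The label applies to all 128 planned infants. Assessment of impairment and cranial ultrasound is protected. Care that may affect death is not, and neither are time to discharge and adverse events to the extent that treating staff record them. No direction or size of bias can be derived. The sample size, the primary outcome and the choice of analysis are unaffected.

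**What to change.** 1. Replace double-blind with outcome-assessor-blind wherever it appears, and state for each role whether it is blinded.
2. State that the discharge neurological examination is scored by the already-blinded paediatric neurologist.
3. Separate list generation from blinded analysis. Alternatively, run the analysis on an A/B-coded file whose key is held by someone outside both care and analysis. State which applies, and say what the Biostatistician sees when monitoring data.
4. Report time to discharge, and any adverse events recorded by treating staff, as assessed without blinding.

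The study was ongoing when the article was submitted, so all four can still be done. The cost is a less favourable design label and minor role assignment. Masking ward staff from now on is a further option but is not part of this fix: it would split the trial into two differently masked cohorts, and the article does not describe how doses are prepared.

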### Intervention and procedure

The approach to the management of HIE in our center is supportive care. Therapeutic hypothermia is not available. Supportive care includes maintaining normothermia, fluid, electrolyte and glucose balance, respiratory support with continuous positive airway pressure (CPAP) and oxygen, control of seizures and management of other complications as they arise [46]. During this study, participants randomized into EPO group, receives 1000 IU/kg of Erythropoietin intravenously statim on admission then daily for 5 days. This dose regimen was modified from the pharmacokinetic study by Wu et al. [37] Placebo/ control group receives 2 ml of 0.9% Saline statim on admission then daily for 5 days.

### Clinical monitoring

All the participants are offered standard care according to the unit protocol for HIE. Fluid and electrolyte balance are maintained, oxygen therapy and other respiratory support modes are provided as necessary. Blood pressure is monitored during drug administrations and subsequently through a non-invasive blood pressure monitoring system. Daily monitoring and assessments are conducted until the 8th day of life using the Thompson’s score [47]. A peak score above 15 predicts a bad outcome, whereas maintaining a score below 10 which becomes 0 at 1 week of age suggests a good prognosis. The following clinical course and baseline characteristics are recorded on a pre-designed proforma: the grade of HIE (moderate or severe), the type of respiratory support needed, the presence of seizures, the time to establishment of full oral feedings through sucking and neurologic examination at discharge; the age at commencement of intervention, place of delivery, sex, gestational age at delivery, birth weight, head circumference, mother’s age, parity and intrapartum events are all recorded.

